#### Patient and public involvement (PPI) statement

2.3.8

Early or delayed start of the rehabilitation program will be randomized for the surgically treated patients. If patients don't want to be randomized, they can choose their preferred starting time of the post-surgical rehabilitation program. Control participants will be recruited through public announcements. Furthermore, patients will be encouraged to recruit controls without any known lumbar spinal impairments from their own environment in order to increase the chance of getting comparable control subjects in terms of sex, age, and activity level. Patients' and controls' will be asked about their experience with the assessments in order to better estimate and compare the exhibited strain and perceived exertion of the functional tests.

## Ethics and dissemination

3

The present study has been approved by the Institutional Review Board of Martin Luther University Halle-Wittenberg (reference number: 2022-128) and Ärztekammer Sachsen-Anhalt (reference number 23/34). Prior to enrolment in the study, all patients will be asked to give their written informed consent. The patient can decide at any time to be released from the study, and they will be made aware of this in the information leaflet. Their data will then be deleted from the data collection file. Voluntary termination of study participation will have no disadvantages for the patients.

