#### Power analysis and sample size considerations

2.3.6

The ODI was set as our primary outcome measure. For this study, we approximated the sample size using a hypothetical approach. In order to estimate the number of cases needed, the ODI results of 46 patients with LSS (41% men) who underwent fusion surgery were used [45]. Considering the mean change from baseline of 16.1 points and the standard deviation of 17.8, a large effect (d = 0.9) can be expected. With a significance level of 5% and a power of 95%, the minimum sample size needed with this effect size is 15 patients with LSS who will undergo fusion surgery [one-sample *t*-test] (G*Power 3.1.9.2). Only 65% (30) of the patients reduced their ODI by at least ten points one year post-operatively [45]. Taking into account that approximately two-third of the patients included will reach the minimum clinically important difference and assuming a relatively high dropout rate of 20%, 30 patients with LSS would have to be initially included in each group.

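### Formal withdrawal erases a patient's whole record, including baseline and completed visits, so withdrawers drop out of the as-randomized and before/after analyses

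*Protocol article*

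**What the plan says.** Section 3 (Ethics and dissemination) sets the trigger: "The patient can decide at any time to be released from the study". The consequence follows: "Their data will then be deleted from the data collection file". The text does not separate data already collected from data still to come, and it does not make deletion depend on a request.

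Three other places bear on this:

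- Section 2.3.6 plans for loss of patients: "assuming a relatively high dropout rate of 20%, 30 patients with LSS would have to be initially included in each group". Dropout is not defined and is not divided into formal withdrawal and loss to follow-up. The figure is used only to raise the number recruited.
- Section 2.3.7 plans mixed models for the early/late comparison, the comparison of treatment groups and controls, and the before/after comparison.
- Section 2.3.8 randomizes surgical patients to early or delayed rehabilitation and lets those who decline randomization choose their timing. Sections 2.1 and 2.3.5 place the measurements from before surgery to 24 months after rehabilitation.

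**The concern.** Withdrawal normally ends further data collection. Here it also removes what has been collected. A patient who leaves shortly before the 24-month visit would lose the pre-operative, start-of-rehabilitation, end-of-rehabilitation, 6-month and 12-month records.

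Three things are at stake:

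- A randomized patient whose record is deleted can no longer be analysed in the allocated group, so the as-randomized set is incomplete.
- A mixed model can use incomplete records, and that is one of its main advantages when patients leave over a long follow-up. For withdrawers there would be no record to use.
- If those who leave have done worse than those who stay, the remaining patients look better than the group as a whole. With the withdrawers' outcomes deleted, the trial could not check whether this happened.

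The rule is stated in the text, so this is not a detail that a condensed article has left out. No analysis plan can restore deleted records.

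**Working it through.** **Step 1. Reproduce the plan's sample size, to see whether the rule disturbs it.**

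Inputs from section 2.3.6: mean ODI change 16.1, SD 17.8, significance level 5%, power 95%, one-sample t-test, 65% of patients with a reduction of at least ten points, 20% dropout.

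- Effect size: 16.1 / 17.8 = 0.904, stated as 0.9.
- Exact noncentral-t power with a one-sided 5% level and d = 0.9: n = 15 gives 95.2%. This matches the stated minimum of 15.
- Inflation: 15 / 0.65 = 23.1, rounded up to 24; 24 / (1 − 0.20) = 30. This matches the stated 30 per group.
- After 20% loss: 30 × 0.80 = 24 remain, and 24 × 0.65 = 15.6, which is still at least 15.

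The 20% allowance already covers the loss in numbers. Deletion does not make the stated size wrong; any harm is selection.

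**Step 2. How many records could be deleted.**

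Deletion is tied to the patient's decision to leave, while 20% is undefined dropout. On the plan's own dropout figure:

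- If every dropout is a formal withdrawal: 0.20 × 30 = 6 per group lose all data. This is the upper bound.
- If half are (assumption): 0.10 × 30 = 3 per group.

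**Step 3. Bias in one group's mean change.**

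Let w be the share who withdraw and D the amount by which their mean ODI improvement falls short of the stayers'. The full-group mean is (1 − w) × stayers + w × (stayers − D) = stayers − wD. The mean among stayers is therefore too favourable by w × D. The documents give no value for D. The range below is assumed; its top, 16.1, is the whole mean change in section 2.3.6.

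| D (points) | w = 20% | w = 10% |
|---|---|---|
| 5 | 1.0 | 0.5 |
| 10 | 2.0 | 1.0 |
| 16.1 | 3.2 | 1.6 |

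**Step 4. Bias in the early/late contrast.**

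The bias is the difference between the two arms' products w × D.

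- Same w and same D in both arms: zero.
- Withdrawal 10% in one arm and 30% in the other (assumption; average 20%), same D: (0.30 − 0.10) × D = 1.0, 2.0 or 3.2 points for D = 5, 10 or 16.1.
- Withdrawal 20% in both arms, D = 5 in one and 16.1 in the other (assumption): 0.20 × (16.1 − 5) = 2.2 points.

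**Step 5. How much of this is recoverable if records are kept.**

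An illustrative simulation assumed SD 17.8, 20% leaving after an earlier visit, and leaving more likely when the observed improvement at that visit was small (logit slope −1 per SD).

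| Correlation between visits | Bias if withdrawers' records are deleted | Bias if the earlier visit is kept and modelled |
|---|---|---|
| 0.4 | +1.2 | below 0.1 |
| 0.6 | +1.9 | below 0.1 |
| 0.8 | +2.5 | below 0.1 |

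The near-complete recovery depends on leaving being driven by a value already observed.

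**The case against.** The strongest objection is to a reading that a reader might easily make: that the rule turns the planned 20% dropout into a completers-only analysis. The documents do not support that. Deletion follows a decision to leave. Nothing says that patients who miss visits or are lost to follow-up have their data removed, and their partial records can stay in the mixed model. This objection stands, and 20% is therefore only an upper bound on the share deleted.

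It would also go too far to say that analysis by allocated group becomes impossible, or that withdrawals cannot be counted by arm. Retained patients can still be analysed as allocated. The rule concerns the data collection file and is silent on enrolment and randomization logs, so counts may survive. Patients who chose their timing have no randomized comparison to lose, and that choice may reduce withdrawal over the waiting time.

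On size, the range rests on assumed differences. The top value amounts roughly to withdrawers not improving at all if stayers improve by the planned mean. With SD 17.8 and 24 retained per group, the standard error is 17.8 / √24 = 3.6 points for a group mean and 17.8 × √(2/24) = 5.1 for a difference, so the bias is below one standard error in every scenario shown. That is fair as scale. However, 3.2 points is about a third of the ten-point reduction used in section 2.3.6, and a systematic error is not reflected in the confidence interval.

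Keeping early visits also does not recover outcomes after withdrawal, and it helps little with patients who leave before any post-baseline visit. This stands and limits what the fix can promise.

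Finally, deletion on withdrawal protects participants, two ethics bodies approved the study, and the leaflet and consent text are not shown. Practice may be narrower than the sentence in section 3. As written, though, that sentence applies to all who leave, and the right to deletion can be kept by granting it on request.

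**Conclusion.** The point holds for formal withdrawal. As written, every patient who leaves by their own decision loses all recorded data without having to ask for it. Such patients are missing from the as-randomized early/late comparison and the before/after analyses, and the planned mixed model cannot use what they contributed.

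The share affected is unknown. It is at most 6 of 30 per group on the plan's own dropout assumption, and 3 of 30 if half of dropout is withdrawal. Assuming withdrawers improve 5 to 16.1 points less, a group's mean change is overstated by 1.0 to 3.2 points at the upper bound and by 0.5 to 1.6 points at 10% withdrawal. The timing contrast is biased only if withdrawal rates or outcome differences differ by arm. That withdrawers do worse is itself an assumption, and one the trial could not test after deletion. The stated sample size does not change.

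The rule should be changed: the loss is irreversible for each patient it is applied to, and baseline data collection began in August 2023.

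**What to change.** Reword the withdrawal rule in section 3, the information leaflet and the consent form:

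- On withdrawal, stop new data collection, but keep and analyse data collected to that date, as covered by consent.
- Delete records only if the patient expressly asks for it.
- Include the retained visits in the mixed models of section 2.3.7.
- Report the number of withdrawals and the number of deletions by group.

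This reduces bias to the extent that leaving depends on outcomes already observed; it does not supply outcomes after withdrawal. The patient's freedom to leave without disadvantage is unchanged.

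The cost is a change of consent wording and an ethics amendment, for which the section on ethical approval and consent already gives a route, including an update of the registry entry. The downside is that patients already enrolled stay under the existing rule unless they consent again, so for a time two rules would apply. Deletions made under the existing rule should be counted by group as well, as far as enrolment records allow.

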## Results

4

The research results from this study will be spread through peer-reviewed publications and scientific contributions at national and international conferences.

## Ethical approval and consent to participate

Institutional Review Board approval was obtained through the Ethics Committee of Martin Luther University Halle-Wittenberg (reference number: 2022-128). Significant changes to the protocol will be submitted as an amendment to the Ethics Committee and updated in the trial registry. All patients will be asked to give their written informed consent. All methods will be carried out in accordance with relevant guidelines and regulations.

## Consent for publication

Not applicable.

## Availability of data and materials

The datasets collected in this study will be available from the corresponding author on reasonable request.

